##### B. What is evaluated for safety

The safety evaluation includes all participants who were randomized and participated in the trial.

##### C. Safety assessment

- Blood tests: blood tests are performed before and after treatment to check for adverse events.
- Cardiovascular system: Blood pressure and pulse rate are measured at each visit.

##### D. Observe adverse events

Participants are trained to voluntarily report information about any adverse events that occurred during the study period, and the investigators verify the presence of adverse events through laboratory tests and questionnaires.

The investigator should evaluate adverse events and record any previously unrecorded adverse events in the appropriate section of the case record, indicating the action taken, the nature of the event, date and time of onset, duration, severity, and relation to acupuncture or electroacupuncture. Any changes in the frequency or severity of adverse events during the study should be recorded on a separate page.

1. Assessing the severity of an adverse event

Based on clinical signs and symptoms of an adverse event, the criteria are as follows

| 1 = Mild | Does not interfere with normal daily life (functioning) to the extent that it is barely noticeable to the study participant.  Mostly not requiring treatment. |
| --- | --- |
| 2 = Moderate | The degree to which the participant is uncomfortable and interferes with normal daily activities (functioning).  The degree to which the particiapant may be able to continue the study but may need treatment. |
| 3 = Severe | The degree to which the participant is so uncomfortable that daily activities (functioning) are not possible and continued participation in the study is not possible.  The extent to which treatment or hospitalization may be required |

1. Evaluating acupuncture and causality

The degree of certainty that an adverse event can be attributed to acupuncture or electroacupuncture (or to other causes, such as the natural history of the underlying condition or concomitant therapies) is determined by how well the adverse event fits the following criteria: the adverse event appeared after starting acupuncture, disappeared after discontinuation, or reappeared upon reuse, indicating that it is related to acupuncture treatment.

1 = Definitely relevant Certain > 90%

2 = Highly relevant Probable/likely > 70%

3 = Possibly related Possible 50%

4 = Not thought to be relevant Unlikely < 30%

5 = Difficult to determine relevance Conditional/ unclassified < 10%

1. Serious adverse events

"Serious adverse event" means an event that meets 1 of the following criteria

A) Causes death or is life-threatening;

B) Requires hospitalization or extended hospitalization.

C) Causes persistent or significant disfigurement or impairment

D) Causes birth defects or abnormalities

Adverse events should also be reported as serious if they are deemed serious by the investigator or if they suggest a significant risk, contraindication, adverse effect, or caution associated with acupuncture or electroacupuncture. Participants who experience an adverse event should be followed by the investigator until the adverse event resolves or stabilizes.

1. Actions taken regarding adverse events

0 = No action taken

1 = Temporary suspension

2 = Stop acupuncture or electroacupuncture interventions

3 = Medications

4 = Non-drug treatments

5 = Extended hospitalization/stay

**E. Reporting**

The principal investigator will educate co-investigators and participants about any adverse reactions that may occur after acupuncture or electroacupuncture interventions and will educate them to report any phenomena that occur after the intervention.

All systemic or pathologic symptoms that occur after acupuncture or electroacupuncture interventions shall be recorded and kept in a case record sheet that conforms to the standards of clinical trial management, including the type, time of occurrence, severity, treatment, therapeutic agent, outcome, and causal relationship to acupuncture treatment.

If a "serious adverse event" occurs during the study, it will be reported to the Institutional Review Board (IRB) to determine whether the study should be continued or discontinued.

1. If participants die during the study or pose a serious risk to life, this will be reported within 7 days of receiving the report, but in this case, further details will be reported within 8 days of the initial report.
2. For all other serious and unexpected adverse events, report them within 15 days of the date the sponsor is informed or becomes aware of them.
3. Additional safety information related to the reporting of the above should be reported by phone or in-person by the investigator until 7 days after the end of the study (washout period).
4. The principal investigator shall conduct all aspects of the study in accordance with the Declaration of Helsinki.

□ Women of childbearing age

①Women of childbearing potential must have a negative urine pregnancy test prior to study entry.

②Women of childbearing potential must be using adequate and reliable contraception for at least 1 month prior to study entry and continue for the duration of the study.

③If you think you may become pregnant during the study, notify the study staff immediately, and the pregnancy test may be repeated.

##### F. What to do if an adverse event occurs

During this study, the investigator and personnel in charge of the study must ensure the safety of the participants, and in the event of a serious adverse event, the study must be stopped and prompt and appropriate measures must be taken to minimize the adverse event.

In the event of a "serious adverse event" during a clinical trial, each person's responsibilities are as follows

1. Principal investigator duties

The principal investigator should immediately report any serious adverse events that occur during the clinical trial to the institutional review board and sponsor and stop all or part of the clinical trial for that acupuncture and electroacupuncture treatment until otherwise instructed.

1. Investigator duties

The clinical investigator shall immediately report any serious adverse events that occur during the conduct of the clinical trial to the clinical investigator in charge and the sponsor.

1. Institutional review board duties

In the event of a serious adverse event, the IRB shall take any necessary action, including ordering the discontinuation of part or all of the study, to the principal investigator.

#### How to evaluate validity and how to interpret

##### Primary outcome variable

- - 1. Visual Analogue Scale (VAS) of coldhypersensitivity in the hands and feet:
- At each visit, a 10 cm long line is drawn and participants are asked to select the number on the line that corresponds to their level of coldness. For the hand visual analog scale, the left end of the straight line is labeled "no hand coldness" and the right end is labeled "most severe hand coldness"; for the feet visual analog scale, the left end of the straight line is labeled "no feet coldness" and the right end is labeled "most severe feet coldness". The score is the number of ruler points at the location of the 'I' in the big box.
- Examine the difference between pre-treatment and post-treatment results for VAS outcomes assessed at each visit, by visit date.

[References]

Ryoo GS, et al. A case report of cold hypersensitivity caused by acute and chronic blood deficiency. The journal of oriental obstetrics & gynecology. 2009;22(2):222-30.

Lee MJ, et al. A clinical case study to evaluate the hot flush and abdominal cold hypersensitivity relief efficacy of Cheonglijagamtang in climacteric women by DITI. Journal of oriental medical thermology. 2010;8(1):26-32.

Cho JY, et al. A case report of cold hypersensitivity of hands and feet patient. The journal of oriental obstetrics & gynecology. 2011;24(3):195-202.

Lee YJ, et al. Effects of far-infrared rediating products on coldhypersensitivity of lower limbs using cold stress test (CST): a pilot study. Journal of oriental medical thermology. 2008;6(1):69-75.

- Visual Analogue Scale (VAS)

Please place an 'I' in the graph below for your average daily hand coldness over the past week

No hand coldness

Most severe hand coldness

0 points 10 points

- Visual Analogue Scale (VAS)Score:

Please place an 'I' in the graph below for your average daily feet coldness over the past week.

No feet coldness

Most severe feet coldness

0 points 10 points

##### Score:

- 1. **Secondary outcome variable**
     1. Body temperature: Thermometer measurement
- The difference in temperature between the bilateral palm (PC8), arm (LU4), anterior thigh (ST32), and dorsum of foot (LR3) regions, measured within 10 minutes of each visit, before the start of treatment and after the end of treatment, respectively, using a thermometer

[figure not shown]

[figure not shown]

[References]

Lee MJ, et al. A clinical case study to evaluate the hot flush and abdominal cold hypersensitivity relief efficacy of Cheonglijagamtang in climacteric women by DITI. Journal of oriental medical thermology. 2010;8(1):26-32.

Kim EG, et al. A clinical case study for the diagnosis and assessment of abdominal cold hypersensitivity treatment by DITI. Journal of oriental medical thermology. 2009:7(1):55-65.

Cho JY, et al. A case report of cold hypersensitivity of hands and feet patient. The journal of oriental obstetrics & gynecology. 2011;24(3):195-202.

Lee YJ, et al. Effects of far-infrared rediating products on coldhypersensitivity of lower limbs using cold stress test (CST): a pilot study. Journal of oriental medical thermology. 2008;6(1):69-75.

- - 1. Quality of Life Assessment Questionnaire (WHOQOL-BREF) and Quality of Life Assessment EQ-5D
- Overall quality of life, general health, physical health, psychological health, social relationships, and environment, measured at visits 1, 10, and 11.
  - 1. Pattern Identification Questionnaire
- Pattern identification questionnaire measured at visit 1 to correlate symptoms and VAS changes in patients with cold feet according to dialectic indicators.
  - 1. Coldness Diagnostic Questionnaire
- Coldness Diagnostic Questionnaire, which asks participants about their subjective or objective symptoms of coldness, is measured at Visit 1, Visit 10, and Visit 11.

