Sensory, musculoskeletal, endocrine, multiple, urinary, reproductive, digestive, cardiovascular, nervous, dermatologic, and estrogenic systems. Obtain a history of renal, hematologic, lymphologic, respiratory, and other medical and medication history. Any significant findings o n examination at the initial visit should be recorded in the other organ systems section of the case record sheet, and any significant medical findings that meet the definition of an adverse event after initiation of the study procedure should be recorded on the adverse event sheet.

- - - 1. Visual Analog Scale (VAS)

Assess at each visit. At each visit, a VAS for the degree of coldhypersensitivity in the hands and feet will be completed by the participants with the assistance of the investigator.

- - - 1. Pattern Identification Questionnaire and Constitutional Diagnostic Questionnaire (KS- 15)

Administered at Visit 0.

Two principal investigators or a Korean medicine doctor will evaluate the participants.

The evaluator checks the items and marks ◯ on the most appropriate item to indicate the degree of the condition the participant has through the pattern.

The evaluator marks the corresponding pattern identification with a ◯.

- - - 1. Vital signs and height and weight measurements

Vital signs are assessed at every visit. Vital signs include blood pressure, pulse rate, and temperature. Height is measured only at Visit 0, and weight is measured at Visits 0, 10, and 11.

- - - 1. Determining conformance to inclusion/exclusion criteria

At Visit 0, consent, demographic and sociodemographic information, medical and medication history, laboratory tests, pregnancy test and chest x - ray, electrocardiogram, and thermometer measurements to determine if the participant meets the cold diagnostic criteria will be taken.

- - - 1. Check for changes in medical and treatment history

Inquire at each visit whether there have been any changes in medical and treatment history since Visit 0 (Screening). Inquire about any changes compared to what was identified in the drug history screening at Visit 0. If there are any changes in concomitant medications, document them in detail in the case record.

- - - 1. Clinical examination items

Obtain written informed consent and perform a 12-lead EKG, chest x-ray, and examination of the following on Visit 0

①Hematological tests: WBC, RBC, Hemoglobin, Platelet

②Blood biochemical tests: BUN, Creatinine, AST, ALT, r-GTP, Glucose

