##### B. Visit 1 (D1)

1. Vital signs and weight measurement
2. Verify medical conditions/medications/treatments (check for changes in medical history and medications)

From Screening to Visit 1, investigate whether any new conditions, additional medications, or additional treatments have occurred. If yes, record in the Conditions/Medications/Treatments CRF form.

1. General physical exam

Determine if the patient has any of the conditions listed on the general physical examination form in the CRF at the time of the visit.

If present, circle yes and record in the abnormal findings section below.

V for none.

1. Thermometer measurements

At each visit, before and after treatment, bilateral temperatures at the anterior thigh (ST32) and dorsum of the foot (LR3), and at palm (PC8) and arm (LU4) will be measured using a non-contact infrared thermometer at a distance of, 3cm for three consecutive measurements and the median value excluding the highest and lowest values will be recorded.

1. Hands and feet coldness Visual Analogue Scale (VAS)

The VAS of coldhypersensitivity in the hands and feet will be completed by the participants with the assistance of the researcher. On the VAS, participants will mark an I for their level of hands and feet coldness.

O, V, not verbalized (to be precise)

1. Coldness diagnostic Questionnaire

Let the paticipants fill in the fields that need to be filled in.

The measurement must be performed by a practitioner.

1. The Korean version of the World Health Organization Quality of Life Scale (Short Form) (WHOQOL-BREF) and the EQ-5D Quality of Life Assessment

Check ◯ only for the most appropriate number.

Paper medical records keep the questionnaire and, if the medical record is electronic, the score, description, or item number. or itemized numbers. If this is difficult, create and store a clinical trial-specific paper medical record file.

1. Randomization

Randomize to no treatment, acupuncture treatment, and electroacupuncture treatment.

Record the predetermined randomization table number in the medical record and CRF.

1. Acupuncture or electroacupuncture

An investigator who does not participate in the survey will administer the treatment to the randomized acupuncture group or electroacupuncture group, respectively.

1. Specify your next visit date

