##### D. Visit 10 (D35±3)

1. Participant dropouts

Calculate treatment adherence for participants.

Example) Treatment Adherence (%) = Participant's actual acupuncture treatments / 10 acupuncture treatments

Adherence to acupuncture treatment: □□.□ %

1. Vital signs and weight measurement

Measure and record vital signs and weight.

For vital signs, check and record body temperature, systolic blood pressure, diastolic blood pressure, and pulse rate.

1. Verify conditions/medications/treatments (check for changes in medical history and medication adherence)

Check for any new conditions, additional medications, or other treatments since visit 9. If so, record in the Condition/Medications/Treatments CRF form

1. General physical exam

Determine if the particiapant has any of the conditions listed on the general physical examination form in the CRF at the time of the visit. If present, circle yes and record in the abnormal findings section below.

V for none.

1. Acupuncture or electroacupuncture

A researcher who did not participate in the survey will administer the appropriate treatment to the randomized acupuncture or electroacupuncture arm.

1. Thermometer measurements

Before and after treatment, bilateral temperatures at the anterior thigh (ST32) and dorsum of the foot (LR3), and palm (PC8) and arm (LU4) will be measured using a non-contact infrared thermometer at a distance of 3cm for three consecutive readings, and the median value excluding the highest and lowest values will be recorded.

1. Visual Analogue Scale (VAS) of coldhypersensitivity in the hands and feet

The VAS of coldhypersensitivity in the hands and feet will be completed by the participant with the assistance of the researcher. On the VAS, participants will mark an I for their level of hands and feet coldness.

O, V, not verbalized (to be precise)

1. Screening for and identifying adverse events

Check for any adverse events that occurred during the study. If so, create an adverse event report in the CRF.

Adverse event reporting procedures are in accordance with the adverse event reporting SOP and the standard operating procedures for acupuncture treatment administration.

1. The Korean version of the World Health Organization Quality of Life Scale (Short Form) (WHOQOL-BREF) and the EQ-5D Quality of Life Assessment

Use ◯ only for the most appropriate number.

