##### How to analyze validity variables

- - 1. Primary efficacy endpoint: Visual Analogue Scale (VAS) coldhypersensitivity in the hands and feet

The primary efficacy evaluation variables will be analyzed using the ITT group as the main analysis group, and the results of the PP group will be presented in addition. Repeated ANOVA, paired t-test, etc. will be performed to test whether there is a difference in the change in VAS score between the no-treatment control group and the acupuncture treatment group or the electroacupuncture treatment group. The comparison of the degree of improvement of VAS scores within each group will be performed by paired t-test using the difference between pre- and post- treatment VAS scores (VAS score at Weeks 5±3 days - VAS score at Visit 1).

- - 1. Secondary Validation Variables
       1. Body Temperature (BT; thermometer measurement): Repeated ANOVA is performed to test whether there is a difference in BT change between the acupuncture treatment group and the electroacupuncture treatment group. To compare the degree of improvement in BT within each group, a paired t-test will be performed using the difference between BT before and after acupuncture treatment (BT at Weeks 5±3 days - BT at Visit 1).
       2. WHOQOL-BREF Quality of Life Assessment Questionnaire: ANOVA and post hoc tests will be used to test the difference between each group. Comparison within each group is done by paired t-test using the difference in values before and after acupuncture treatment (value at Weeks 5±3 days - value at Visit 1).
       3. Pattern Identification Questionnaire:
          - This figure shows the distribution of the dialectical observables (dialectical indicators) in participants with coldhypersensitivity in the hands and feet. To determine the relationship between the dialectical indicators and the change in symptom VAS, an ANOVA test (non-parametric test if not normally distributed) and post hoc tests are performed for each indicator with the change in symptom VAS as the dependent variable.
          - Validity and reliability of the basic instrument are evaluated. The validity evaluation is

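### The temperature outcome is a between-region difference read around each session in one section and an unspecified BT change to Week 5 in another, so it is never one score that exists in all three arms

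*Protocol*

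**What the plan says.** **Outcome definition.** Under secondary outcome variables, in the section on how validity is evaluated, the Protocol defines body temperature as "The difference in temperature between the bilateral palm (PC8), arm (LU4), anterior thigh (ST32), and dorsum of foot (LR3) regions". On timing, the same item adds that this quantity is "measured within 10 minutes of each visit, before the start of treatment and after the end of treatment, respectively, using a thermometer".

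**Visit procedures.** The Visit 1 text has "At each visit, before and after treatment, bilateral temperatures at the anterior thigh (ST32" and the other three sites recorded. The text for Visits 2 to 9 repeats this, and Visit 10, which includes a treatment session, has "Before and after treatment, bilateral temperatures at the anterior thigh (ST32) and dorsum of the foot (LR3), and palm (PC8) and arm (LU4" recorded again. At Visit 11, where no session takes place, the before-and-after wording is absent.

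**Analysis.** Under How to analyze validity variables, the within-group paired t-test uses "the difference between BT before and after acupuncture treatment (BT at Weeks 5±3 days - BT at Visit 1". The between-group test is a repeated ANOVA of BT change for acupuncture against electroacupuncture. The statistical row of the Clinical Protocol Overview says the same.

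**Comparison intended.** The Secondary purpose section lists body temperature among the outcomes whose changes are compared between all three arms.

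**Control arm.** It receives no needling and attends Visits 1, 10 and 11. The schedule gives it thermometer readings at screening and at those three visits.

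**The concern.** The outcome section and the analysis section do not describe the same score. The first gives a difference between regions, with readings around each session. The second gives one BT value and a change over the course. The phrase about before and after treatment refers to a single session in the visit sections, and most naturally in the outcome section too. In the analysis section it refers to the five weeks.

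Two things are at stake. First, treated participants have two thermometer readings on the day of Visit 10 and two on the day of Visit 1, and the text does not say which pair forms the change. Some pairs contain the immediate response to a session as well as any lasting effect. Second, the definition built around a session has no counterpart in the no-treatment arm, although the Secondary purpose section says that arm is part of the comparison.

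**Working it through.** The Protocol states no figure for this endpoint, so there is none to reproduce. The check compares the sections and counts the scores they allow.

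**1. Quantity**
- Outcome section: a difference between regions. It does not say which region is subtracted from which, or how left and right are combined.
- Analysis section and overview: BT, with no region, side or difference named.

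**2. Timing**
- Outcome section and the Visit 1 to Visit 10 procedures: before and after treatment at each visit.
- Analysis section: "BT at Weeks 5±3 days - BT at Visit 1", with no choice between the two readings taken on each of those days.

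**3. What each choice estimates in a treated participant.** Write C for the change in the pre-session reading from Visit 1 to Visit 10, and s1 and s10 for the post-minus-pre change at sessions 1 and 10.

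| Week 5 reading | Visit 1 reading | Difference |
| --- | --- | --- |
| pre | pre | C |
| post | pre | C + s10 |
| post | post | C + s10 − s1 |
| pre | post | C − s1 |

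Only the first row is free of session effects. The second row is the literal reading of before and after treatment. Between the two needling arms it is biased by the difference in s10 between them. Against controls it would be biased by the whole of s10. The documents give no value for s1 or s10, so the bias cannot be sized.

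The order of steps in the visit text makes the second row a plausible choice. At Visit 1 the thermometer step is listed before randomization and treatment; at Visit 10 it is listed after the treatment step. The list order is not stated to be the order of performance, so this is suggestive only.

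**4. Number of scores that fit the text**
- Readings per time point: 4 sites × 2 sides = 8, hence 8 × 2 = 16 per session in treated participants and 8 per visit in controls.
- If the regional differences are the two used for eligibility (palm–arm and thigh–foot, an assumption): 2 × 2 sides = 4 gradients. With three timings (pre, post, post minus pre), 4 × 3 = 12 scores.
- If BT is a single-site temperature: 8 × 3 = 24 scores.
- In controls there is one timing, so 4 gradients or 8 single-site scores.

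**5. Availability by arm**
- Session pairs: up to 10 per treated participant, 0 per control. Controls are 24 of 72 participants, or 33%.
- One reading at each of Visits 1, 10 and 11: present in all three arms.

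A score that works in every arm is therefore already being collected; the text does not select it.

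**6. Arms compared.** The Secondary purpose section names three arms. The between-group BT test names two, and its time points are not listed.

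**The case against.** The best defence is that these passages complement each other. Both the outcome section and the analysis section label the variable as a thermometer measurement. BT can thus be read as the regional difference, with the outcome section supplying the quantity and reading times and the analysis section supplying the contrast. The general principles also make baseline-to-end change the basic method. On this view the rest (sides, pairs, which reading) is detail for a statistical analysis plan that is not shown, and two figures after the definition, also not shown, may bear on it.

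Part of this stands. Nothing says that BT is a raw site temperature. A reader might infer that the two definitions run in opposite directions, improvement being a rise in one and a fall in the other; that holds only if BT is raw, and the Protocol does not say so. A reader might also infer confusion with the vital sign, since "Vital signs include blood pressure, pulse rate, and temperature". The schedule and the visit lists keep vital signs and the thermometer measurement as separate items, so that is not supported. Nor is it true that temperature cannot be analysed in controls. Only the session-based version is missing there, and the between-group BT test as written does not use controls.

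The defence does not remove the rest. The same phrase has two meanings within the Protocol, the choice of same-day reading changes what is estimated, and the two-arm test does not deliver the stated three-arm comparison.

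**Conclusion.** The point holds as an inconsistency within the Protocol. The temperature outcome is never fixed as one score available in all three arms, and the analysis wording allows the immediate effect of session 10 to enter the five-week change.

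Its size is structural: four possible pre/post pairings, only one of them free of session effects, and no session-based value for 33% of participants. How far results would move depends on s1 and s10, which the documents do not give.

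The counts of 12 and 24 show how open the definition is. A reader might turn them into a false-positive rate by treating the readings as independent tests. That is not supported: the readings come from nearby sites on the same person and are correlated. The endpoint is also secondary, with no role in the sample size or the primary test. Nor should the point rest on temperature being the only outcome that participants do not rate themselves, because the pattern identification questionnaire is completed by an evaluator.

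The conclusion assumes that before and after treatment in the outcome section refers to the session, which the wording about each visit and the visit procedures support. If that section meant only the whole course, the regional difference would still be missing from the analysis text and the same-day reading would still be unspecified. The correction should be made before the data are analysed.

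**What to change.** Use one definition in the overview, the outcome section and the analysis section:
- **Score:** two skin-temperature gradients on the site pairs already used for eligibility, arm minus palm (LU4 − PC8) and thigh minus foot (ST32 − LR3), with left and right averaged.
- **Reading:** the pre-session reading in the needling arms and the single visit reading in controls.
- **Contrast:** Visit 10 minus Visit 1, with Visit 11 minus Visit 1 as follow-up.
- **Comparison:** all three arms, as the Secondary purpose section states, using the visits common to all arms.
- **Descriptive only:** post-session readings, within-session changes and single-site temperatures.

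The cost is wording, since every reading needed is already scheduled. The one loss is that single-site and immediate post-session results become descriptive.
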